## Assignment of interventions: blinding

### Who will be blinded {17a}

Recruiters will be blinded at the time of recruitment to treatment assignment given that assignment will happen only after recruitment is completed. The data analysts will also be blinded to treatment assignment.

### Procedure for unblinding if needed {17b}

If active suicidality emerges, the participant will be flagged and reported to the principal investigator (PI) and university clinical liaison, the latter of which will call the student to assess risk and provide additional support.

## Data collection and management

### Plans for assessment and collection of outcomes {18a}

The baseline, follow-up, and needs assessment surveys will be self-report scales administered online through the Qualtrics platform. The survey program uses complex skip logic, developed for this study, based on participants’ responses to the questions to reduce respondent burden and increase completeness and accuracy of responses.

#### Baseline survey overview

The baseline survey will include questions of 6 types: (i) basic socio-demographics, (ii) CMDs, (iii) impairments associated with CMDs, (iv) current and past treatment of these disorders, (v) COVID-19 experience, (vi) eHealth literacy and use of digital interventions, and (vii) constructs found in previous research to be significantly prescriptive predictors of heterogeneity of CMD treatment response (see Table 2).

**Table 2 Tab2:** Constructs^a^ found to be prescriptive predictors of CMD treatment response in two or more studies

**I. Socio-demographics**: Female, low parent education, marital status, distance of school from permanent residence, living arrangement while at school, employment while at school	
**II. Behavioral health history, triggers, and symptoms:** Symptoms of generalized anxiety disorder, panic disorder, separation anxiety disorder, social phobia, post-traumatic stress disorder, major depressive disorder, adjustment disorder with anxiety and/or depressed mood, insomnia, multimorbidity, history of suicidality, early age of onset, chronicity, high baseline severity, endogenous (depression), number prior/recurrent episodes, high psychomotor symptoms/low energy (depression), avoidance (experiential and behavioral), fear of negative evaluation, role impairment, personality disorder (Borderline Cluster C), psychotic-like symptoms	
**III. Stress and adversity:** Childhood maltreatment/trauma, parental bonding, high stress, interpersonal loss, poor physical functioning, poor cognitive functioning, poor social functioning, poor social support/relationships	
**IV. Personality traits/temperament:** Agreeableness, alexithymia, anxiety sensitivity, attentional control, attributional style, catastrophic cognitions, conscientiousness, cognitive distortions, emotional regulation, extraversion, hopelessness, low openness to experience, negative affect/neuroticism, non-secure attachment style, perceived control, stress reactivity, temperament	
**V. Treatment engagement and related constructs:** Adherence, health literacy, preferences for type of treatment, therapeutic alliance	
**VI.** Other: High cognitive dysfunction/low intelligence	

^a^See [60–64] for reviews of relevant studies

#### Needs assessment survey overview

The needs assessment surveys will include questions that overlap with, but are not identical to, those in the baseline survey: (i) basic socio-demographics; (ii) CMDs; (iii) impairments associated with CMDs; (iv) current and past treatment of mental disorders; students who have not been in treatment at all in the past 12 months will be asked if they ever had a need for treatment in the past 12 months and if they say yes, then they will be asked why they did not seek treatment (barriers) and will be offered enrollment in the trial; and (v) the prescriptive predictors of heterogeneity of CMD treatment response, the same as those administered in the baseline survey of the main trial (see Table 2).

#### Content of specific sections

##### (i) Socio-demographics

These will include sex, marital status, sexual orientation, distance of permanent residence from school, living arrangements, and employment, all of which are hypothesized based on previous research to be prescriptive predictors of CMD treatment response.

##### (ii) CMDs

MDD and GAD will be the primary foci of the intervention. The assessments of the primary outcome disorders will be the widely used PHQ-9 (depression) [44] and GAD-7 (anxiety) [45] scales. Clinical thresholds will be scores of 10+ on the PHQ-9 [65], 10+ on the GAD-7 [45], and 20+ on the recently-developed PHQ-ADS [46]. Eligibility for the trial will require students either to meet criteria for one or both of these disorders or of the PHQ-ADS. However, we will also evaluate other DSM-5 disorders: panic disorder, social phobia, binge eating disorder either with or without purging, PTSD, insomnia, bipolar disorder, adult ADHD, and frequency and quantity of alcohol and drug use (cannabis, cocaine, any other street drug, or a prescription drug either used without a prescription or used more than prescribed to get high, buzzed, or numbed out). Although a larger set of disorders is used in the face-to-face WMH surveys [66], the 9 in the WMH-ICS surveys include those associated with highest role impairment among college students [1]. Bipolar disorder will be assessed with the CIDI-SC [51, 52, 67] only for lifetime prevalence and, as noted above, will be exclusionary for the trial. We will also ask if they have ever been diagnosed with schizophrenia or psychosis as an exclusionary criterion. The other 8 disorders will be assessed either for lifetime (binge-purging disorders), 2-week (PHQ-9, GAD-7), 6-month (ADHD), or 30-day (the other disorders) prevalence. The baseline survey will also assess lifetime prevalence and course of GAD, MDD, and PTSD based on these being hypothesized prescriptive predictors of treatment response (Table 2). Panic disorder will be assessed with the CIDI-SC [51, 52], social phobia with DSM-5 diagnostic criteria [53], binge/purge with the PRIME-MD PHQ [54], PTSD with the six-item short-form PCL-5 screening scale [55], insomnia with a reduced version of the ISI [56], and ADHD with the Adult Self-Report Scale-V1.1 (ASRS-V1.1) [68] screener. Modified versions of the C-SSRS [57] and the SITBI [58] will also be used to assess suicidal ideation, plans, and attempts. As noted above, suicidality with intent (i.e., a current suicide plan with intent to act on the plan) will be exclusionary for the trial.

##### (iii) Impairments due to CMDs

Impairments due to CMDs will be assessed with the SDS [50].

##### (iv) Current and past treatment

Treatment of CMDs will be assessed with the treatment section of the World Health Organization (WHO) Composite International Diagnostic Interview (CIDI) [69].

##### (v) COVID-19 experience

A cross-national team of researchers convened by WHO developed a COVID-19 question battery to assess the experiences of university students around the world with COVID. Questions include having ever been diagnosed with COVID-19, knowing someone who died of COVID-19 and their relationship with the student, and stress the pandemic has caused in different areas of their life.

##### (vi) eHealth literacy and use of digital interventions

This will be assessed with the eHEALS: The eHealth Literacy Scale [70] as well as additional items developed for this study to measure reasons for using digital mental health interventions and preferred features of these interventions.

##### (vii) Prescriptive predictors

Our prescriptive predictor battery was developed by carrying out a systematic literature review of prescriptive predictors of heterogeneity of CMD treatment response with respect to CBT in randomized controlled trials, uncontrolled treatment trials, and prospective observational studies of pre-treatment predictors of treatment response. Replicated significant associations were found for more than two dozen baseline patient self-reported constructs. Space restrictions preclude us from reviewing this voluminous literature, but key constructs are summarized in Table 2 along with references to key review papers. Based on these results, we carried out a second systematic review of best available short-form measures of each construct. We worked with psychometricians in secondary analyses to create new short-form versions of existing scales when none existed [51, 55, 67, 68, 71–73]. It is noteworthy that no prior trial included more than a few of these constructs, making it impossible to know if any of them is significantly independent of the others. Ours will be the first study to include a comprehensive baseline assessment of these constructs.

#### Additional measures used in the treatment trial follow-ups

The 90-day and 12-month follow-ups will focus on both process and outcome measures.

##### Process measures

Process measures will include treatment initiation and type (given that students in all arms will be free to obtain treatment other than our iCBT) using questions from the CIDI [69], satisfaction with treatment based on questions adapted from the Client Satisfaction with Treatment Questionnaire-8 (CSQ-8) [74] and additional items developed for this study, and measures extracted from the *SilverCloud* logs for patients randomized to iCBT to determine the number of logins, time spent overall and per session, and number of modules entered.

##### Outcome measures

These were described above.

### Plans to promote participant retention and complete follow-up {18b}

Participants will be given a gift card worth $15 for completing the 90-day follow-up and another gift card for the same amount for completing the 12-month follow-up. Email reminders will be sent 2 and 4 days after the initial invitation email and we will then make phone calls over the next week in an effort to encourage students to complete the follow-up survey.

### Data management {19}

The Instituto Nacional de Psiquiatría Ramón de la Fuente Muñiz [National Institute of Psychiatry Ramón de la Fuente Muñiz] (INPRFM) study team will maintain a master dataset for all participants who were referred to the project for recruitment along with a record of whether they withdrew before or after completing the baseline survey or after initiating the intervention, were considered ineligible for participation, or were terminated from the study or completed the study. Protection of student privacy with respect to survey data will be achieved by assigning each participant a study identification number and then creating a separate de-identified file for sharing with the Harvard study team and for archiving. All data analyses will be carried out with the de-identified data file. In addition, data cleaning programs will be run to look for implausible or inconsistent answers.

### Confidentiality {27}

Access to personal information of participants will be restricted to relevant INPRFM study staff. Only when there is serious risk of suicidality will information be reported to the university clinical liaison.

### Plans for collection, laboratory evaluation, and storage of biological specimens for genetic or molecular analysis in this trial/future use {33}

Not applicable as no biological specimens were collected as part of this trial.

## Statistical methods

### Statistical methods for primary and secondary outcomes {20a}

#### Analysis of aggregate intervention effects

Aggregate differences in outcomes across arms will be estimated using an intent-to-treat (ITT) [75] analysis approach as well as using a complier average causal effect (CACE) [76] analysis approach. ITT estimates the impact of intervention among all students offered the intervention whether or not they participated. CACE, in comparison, estimates the impact of intervention only on the students who participated in iCBT. To estimate CACE, we will use two-stage least squares (2SLS) [77] and control function procedures [78]. To test the validity of the instrumental variable (IV) assumption in 2SLQ, we will assess balance in the covariate distributions across groups generated by the IV. We will also conduct sensitivity analyses to detect violations of the “independence to unmeasured confounders” assumption, the “exclusion restriction” assumption, and the “monotonicity” assumption as described by Baiocchi et al. [79]. Inverse probability weights (IPW) will be used in all these analyses to deal with loss to follow-up [80].

For each of the two outcome assessments (i.e., 90-day and 12-month), probability of a student being in the study at time *t* will be calculated conditional on information collected as of time *t − 1*. Flexible, nonparametric estimation methods will be used for confounder control [81]. The IPW as of time *t* will be based on the product of these conditional probabilities up through *t*. The treatment-specific mean outcome will be estimated using these weights for the individuals whose outcomes were observed at *t*. Under a coarsening at random assumption, this estimator converges with increasing sample size to the treatment-arm-specific mean outcome that would have been observed had all individuals remained in the study up through *t* [82]. This assumption is closely related to the strong ignorability assumption commonly used in observational studies [83]. Generalized linear models (GLMs) will be used to estimate ITT effects on continuous outcomes, making use of standard visual diagnostics to choose appropriate link functions and error structures [84].

We will report adjusted mean differences (AMDs) with design-adjusted 95% CIs (confidence intervals) and use Poisson regression with robust variance estimation for binary outcomes and report adjusted prevalence ratios (aPRs) with 95% CIs. We will calculate numbers needed to treat (NNTs). When data are missing, we will provide thorough summaries of reasons for missingness and proportions of missing data, test for differences in the characteristics of patients with and without missing data, and describe these and the implications of missing data for interpretation when we report results. As our IPW approach to missing outcomes data will be based on a missing-at-random (MAR) assumption, sensitivity analysis will be carried out based on the weaker missing-not-at-random (MNAR) assumption using pattern mixture modeling [85] in a generalized mixed model framework [86]. The predictors of success in obtaining outcome data at time *t* will include information obtained in prior waves of data collection along with data on intensity of efforts needed to obtain outcome data in a discrete-time survival framework (i.e., in response to the 1^st^, 2^nd^, or 3^rd^ telephone attempts). A range of assumptions about the distribution of the missing data will be made in this approach to investigate sensitivity of results [87]. We will record and report distributions and correlates of dropout and account for all patients in reports.

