### Participant timeline {13}

The participant timeline for each of the three trials is outlined in Fig. 1. Once students are identified through one of the three recruiting methods, they will be sent through email the study invitation, consent form, and baseline survey. Those who are not eligible to participate will be followed up by the clinical liaison at their university and provided the appropriate treatment. Those who are eligible will be randomized to one of the three treatment arms and will subsequently be asked to complete follow-up surveys at 90 days and 12 months after randomization. In the second- and third-year trials, participant flow is similar except that 25% of eligible participants will be randomized according to the PTR generated from the first-year pragmatic trial short-term and long-term effects in years 2 and 3 respectively and the remaining 75% will be randomized with equal allocation into the three treatment arms. The schedule of enrollment, intervention, and assessments for the three trials is outlined in Fig. 2.

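### The 12-month weights multiply the 90-day and 12-month response probabilities but are applied to everyone observed at 12 months, which biases the arm means if students who missed the 90-day survey return

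*Protocol article*

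**What the plan says.** The rule is in the Protocol article, Analysis of aggregate intervention effects {20a}, and is repeated in the section on non-adherence and missing data {20c}. It has four parts.

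- **Modelled quantity.** For each of the two assessments, the "probability of a student being in the study at time" t is estimated from information available at the preceding time point.
- **Weight.** The weight at t "will be based on the product of these conditional probabilities up through" t. At 12 months that is the 90-day probability times the 12-month probability.
- **Who is weighted.** "The treatment-specific mean outcome will be estimated using these weights for the individuals whose outcomes were observed at" t. Observation at the earlier wave is not required.
- **Claimed property.** Under coarsening at random, the estimator is said to converge to the arm-specific mean "outcome that would have been observed had all individuals remained in the study up through" t.

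The same section describes the missingness model as containing "The predictors of success in obtaining outcome data at time" t, so the modelled event is survey response.

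On follow-up, Participant timeline {13} says eligible students "will subsequently be asked to complete follow-up surveys at 90 days and 12 months after randomization". The retention section {18b} gives a gift card for the 90-day survey and "another gift card for the same amount for completing the 12-month follow-up". Section {20c} plans to pursue non-respondents. No section ends 12-month contact after a missed 90-day survey, and none limits the 12-month analysis to 90-day responders.

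**The concern.** The product of the two probabilities is the chance of completing both surveys. Its inverse is therefore the right weight for students who completed both. It is not the right weight for the larger group who completed the 12-month survey, some of whom may have skipped the 90-day one. The two groups coincide only under monotone dropout.

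The text combines the both-waves weight with the larger group and then asserts consistency for the full-retention mean. With intermittent response, that assertion fails even when data are missing at random and both probability models are perfectly estimated. Symptom reduction and remission at 12 months are primary outcomes (Outcomes {12}), and these weights are to be used in both the ITT and the CACE analyses.

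**Working it through.** The document gives no figure to reproduce, so the check is algebra plus worked cases. All response rates below are assumptions. The overall remission rates of 27.5% and 17.5% are the protocol's own planning values (Sample size {14}); their split by stratum is assumed.

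**Algebra.** For students with baseline profile X, let p1 = P(observed at 90 days), a = P(observed at 12 months given observed at 90 days) and b = P(observed at 12 months given missed at 90 days). Weight every 12-month responder by 1/(p1 × own 12-month probability). The expected weight mass at X is

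p1·a/(p1·a) + (1 − p1)·b/(p1·b) = 1 + (1 − p1)/p1 = 1/p1.

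It should be 1. It is 1 if nobody returns (b = 0, so the second term is absent) or if only both-wave responders are used. Otherwise profiles with low p1 are over-weighted.

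**Case 1.** Two equal strata, with 90-day response 80%/50%. Response at 12 months is 85%/70% after a 90-day response and 40%/30% after none. Remission at 12 months is 40%/15%, so the true mean is 27.5%.

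- Responders at 12 months: 0.80 × 0.85 + 0.20 × 0.40 = 0.76, and 0.50 × 0.70 + 0.50 × 0.30 = 0.50; average 0.63.
- Unweighted mean: (0.76 × 0.40 + 0.50 × 0.15)/1.26 = 30.1%.
- Literal rule: masses 1/0.80 = 1.25 and 1/0.50 = 2.00, so (1.25 × 0.40 + 2.00 × 0.15)/3.25 = 0.80/3.25 = **24.6%**. The weights over-correct by 2.9 points. Without normalization the weighted total is 0.5 × 0.80 = 40.0%.
- If the second factor is instead fitted in 90-day responders and used for everyone, the masses are 0.76/0.68 = 1.118 and 0.50/0.35 = 1.429, and the mean is 26.0%.
- Product weights on both-wave responders only: 27.5%. These are (0.68 + 0.35)/2 = 0.515 of the arm, so 0.115/0.63 = 18% of 12-month responders are discarded.
- Own 12-month probability alone, all 12-month responders: mass p1 + (1 − p1) = 1, mean 27.5%.

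**Case 2, milder.** 90-day response 80%/60%, then 80%/70% or 40%/30%. Literal rule: (1.25 × 0.40 + 1.667 × 0.15)/2.917 = 25.7%, off by 1.8 points. With the second factor from 90-day responders it is 26.7%, off by 0.8. Restriction to both waves discards 16%.

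**Where the bias disappears.** Monotone dropout gives 27.5%. With 90-day response equal in both strata (65%/65%), the normalized mean is also 27.5%.

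**Treatment contrast.** True difference 27.5% − 17.5% = 10.0 points, with TAU remission 27.5%/7.5%.

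| Response pattern | Unadjusted difference | Stratum-adjusted difference | Stratum-adjusted prevalence ratio (true 1.57) |
|---|---|---|---|
| Case 1 in both arms | 24.6 − 15.2 = 9.4 | 9.4 | 1.62 |
| Case 1 in iCBT; 90-day response flat at 70% in TAU | 24.6 − 17.5 = 7.1 | 9.7 | 1.59 |

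**Simulations.** In a simulation of 4 million records (continuous outcome, SD 1, missing at random, 64% responding at 90 days and 63% at 12 months) the true mean was 0.00. Product weights on all 12-month responders gave +0.14. Product weights on both-wave responders gave 0.00 with 22% of 12-month responders discarded, and the 12-month probability alone gave 0.00. Effective sample sizes for the last two were 0.424N and 0.544N, so the restriction raises the standard error by √(0.544/0.424) = 1.13, about 13%. A separate simulation with missingness driven only by measured baseline severity gave arm biases of 1.0 to 2.1 points.

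**The case against.** The strongest reply is that the text speaks of being, and remaining, in the study. If that means retention, dropout is monotone and the product is exact. No sentence says outright that 90-day non-responders are contacted again; this is inferred from the timeline, the separate incentives and the pursuit of non-respondents. The inference still holds. The same formula supplies the 90-day weight, which corrects survey non-response only if the phrase means observed at 90 days. The missing-data text also names the modelled event as obtaining outcome data. The discrete-time survival framework mentioned there concerns telephone attempts and does not make response monotone across waves. The MNAR sensitivity analysis relaxes a different assumption and leaves the weight unchanged.

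A second reply is that an article may leave intermittent missingness to a fuller plan. That would answer an omission. Here the article states a rule, the population it applies to and a convergence claim, and the three do not fit together.

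Three limits stand.

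- The planned effect measures are adjusted, and severity is a randomization stratifier, so contrasts can be affected much less than arm means.
- Restricting the product weights to both-wave responders is valid under its own missing-at-random assumptions and costs only precision, so it is not an error.
- A reader might infer that the 12-month precision treatment rule is biased as well. The document does not support this: the weights are tied to ITT and CACE, and the value of the rule is estimated by CV-TMLE with its own regressions and conditional probabilities.

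**Conclusion.** The weighting rule as written is wrong for 12-month outcomes once any student who missed the 90-day survey answers at 12 months. It then does not have the convergence property claimed for it, and it biases the 12-month arm means in the ITT and CACE analyses towards student types with low 90-day response.

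The size cannot be derived from the document. It depends on how many students return and how strongly 90-day response is related to the 12-month outcome. Under the assumed rates, arm remission is off by about 1 to 3 points. The contrast moves from 10.0 to 9.4 points with a shared response pattern, and to 7.1 with differing patterns and no adjustment. It would be too strong to conclude that the treatment effect is seriously distorted, because adjustment for severity brings the 7.1 back to 9.7. The 90-day analysis is unaffected.

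**What to change.** In {20a} and {20c}, replace the product with a direct model for the later wave: the 12-month weight is 1/P(observed at 12 months | arm, baseline, 90-day response indicator, 90-day scores where observed), fitted to all randomized students, with every 12-month responder kept. The cost is about two sentences, with no new software. The downside is that 12-month missingness among students who missed the 90-day survey must be ignorable given arm and baseline data alone.

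Alternatively, keep the product weights and state that they apply only to students observed at both waves. This needs 90-day response to be ignorable for the 12-month outcome given arm and baseline, and it loses precision: 16 to 22% of 12-month responders in the cases above, and a standard error about 13% larger in the simulation. Because the two approaches rest on different assumptions, one could be primary and the other a sensitivity analysis. The text should say which.
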